### Data processing

All collected data will be anonymised, stored, and saved in the main computer, password protected. Data processing will be performed in Vicon Nexus. All markers will be labelled, and marker trajectories were filtered using a fourth order low-pass Butterworth filter via dynamic plug-in gait model with 6 Hz cut-off frequency. Gait identification will be achieved through visual inspection of foot strike and toe off for consecutive strides over the 60s. A threshold of 20 N in ground reaction force will used to determine initial contact and toe-off. Kinetic variables will be normalized using base factors of gravitational constant g (9.81 m/s^2^), leg length, L (m), and body mass, M (kg).

Wearable device data (DANU Sport and DorsaVi ViMove2) will be processed as per the manufacturer’s guidelines, whereas the Axivity AX6 data processing will be carried out from the nine axis (accelerometer, magnetometer, and gyroscope) raw signal by a previously validated in-house algorithm [47]. A master data table will be created with all available outcomes, categorised by subject and date, including a column to indicate distinguishing factors (e.g., those with previous injury history, different performance levels).

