### Equipment

#### Reference standard: 3D motion analysis

A 14-camera motion analysis system (VICON, Oxford, UK), sampling at 250Hz will be used. Calibration of the Vicon system will be conducted before each data collection. Sixteen reflective markers will be placed on the participants lower limb before testing, and a static calibration trial will be initially collected to form a musculoskeletal model [25]. Using a small amount of double-sided tape, the place of markers will be attached bilaterally to the following landmarks: anterior superior iliac spine, posterior superior iliac spine, mid-lateral thigh, lateral knee joint line, lateral mid-shank, lateral malleoli, calcaneal tuberosity, and base of the second metatarsal.

The participants’ specific information of weight, height, ankle width, knee width, and leg length (from posterior iliac spine to medial malleolus) will be measured in the lower body model [26]. The Plug-in-Gait (PiG) lower body model will be used to analyse movement at the joints and evaluate all parameters. The lower body will be modelled as seven segments (one pelvis, two thighs, two shanks, and two feet). A normal gait cycle will be defined from the initial heel-to-heel contact with the same limb. Additional information of the PiG calculations can be found on Vicon’s website. Fig 2 shows the participants’ setup of the anterior, lateral, and posterior views with the markers in place.

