**Fig 3 pone.0291289.g003:**
[figure not shown]
Axivity AX6.

*DorsaVi ViMove2*. The DorsaVi ViMove2 consists of two IMUs modules, each comprising a tri-axial accelerometer (±16g) with tri-axial magnetometer and tri-axial gyroscope (±250°/s), sampling at 100Hz. Modules will be placed onto the anterior surface of the mid-shank of the right and left tibia, as per manufacturer’s guidelines (Fig 4) [29]. Tibia sensor placement is based on the anthropometric measurement of height and a ruler is used to measure exact placement, which is the midpoint between the knee and ankle along the anterior surface of the tibia [30]. After placement of bilateral tibia sensors, the DorsaVi ViMove2 is calibrated via its ViPerform software. Data are transmitted through wireless channel to a recording and feedback device, from which data can be offloaded onto PC for further analysis.

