**Fig 4 pone.0291289.g004:**
[figure not shown]
DorsaVi ViMove2.

*DANU sports system*. The DANU Sports System (Fig 5) is a pair of textile socks, to be worn on both feet. Each sock contains 15 silicone based capacitive pressure sensors, and an IMU module attached onto the anterior surface of the mid-shank of tibia. Each IMU module is Bluetooth enabled for data transmission and is comprised of two configurable tri-axial accelerometers (Accelerometer 1 ±2g, ±16g, and ±32g, Accelerometer 2 ±50g, ±100g, and ±200g), gyroscope (±2000°/s), magnetometer, and with variable sampling rates (60 – 250Hz). The IMU module includes in-built memory for data collection. For this protocol, the DANU Sports System will be configured to a default sampling rate of 250Hz, ±16g, ±50g accelerometers and ±2000°/s gyroscope. Data is collected via Bluetooth on Apple devices 2018 or later (iPad or iPhone devices are required to have at least Bluetooth 5.0 connectivity), and data processing is run through a custom-made Apple application for real-time feedback and visualisation.

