### Outcome measures

The primary outcome measures for this study are running gait outcomes as measured by the wearables and are described in Table 2. A secondary outcome measures is usability. Usability refers to the effectiveness, efficiency, and user satisfaction rating of a product (various grades of wearables) in an particular environment by a user for a specific purpose (running gait analysis) [40].

**Table 2 pone.0291289.t002:** The primary outcomes measured by each grade of wearable.

Outcome	Definition	Axivity AX6	DorsaVi ViMove2	DANU Sports System	Reference Measure

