** *Kinetic* **					
Tibial Acceleration	Acceleration of the tibia, including peak positive acceleration, gradient, slope, magnitude, loading rate etc.	X	**✓**	**✓**	3D Motion capture

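### One 6 Hz low-pass filter on all marker data makes motion capture an unsuitable sole reference for tibial acceleration, a primary outcome

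*Protocol article*

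**What the plan says.** - **Filter.** Data processing gives a single setting for the camera data: "marker trajectories were filtered using a fourth order low-pass Butterworth filter via dynamic plug-in gait model with 6 Hz cut-off frequency". No outcome is exempted. The section on 3D motion analysis says that the Plug-in-Gait model serves for every parameter, so the text shows no separate path for tibial acceleration.
- **Outcome.** Table 2, under Kinetic, defines tibial acceleration as "Acceleration of the tibia, including peak positive acceleration, gradient, slope, magnitude, loading rate etc". Its reference is "3D Motion capture" and nothing else. DorsaVi and DANU are ticked; AX6 is marked X.
- **Status.** Outcome measures states: "The primary outcome measures for this study are running gait outcomes as measured by the wearables", and refers to Table 2.
- **Sampling.** The cameras: "sampling at 250Hz will be used". DorsaVi: "tri-axial gyroscope (±250°/s), sampling at 100Hz". DANU: "configured to a default sampling rate of 250Hz, ±16g, ±50g accelerometers".
- **Wearable processing.** DorsaVi and DANU data follow the manufacturers' guidelines. No filter matched to the reference is mentioned.
- **Comparison.** Under Statistical analysis, wearable and reference are compared by absolute difference, Pearson's r, ICC, Bland-Altman plots with 95% limits of agreement, and RMSE, in 40 laboratory participants.

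**The concern.** The acceleration of the shin at foot strike is a short pulse. If it lasts a few tens of milliseconds, much of its content lies above 6 Hz. Acceleration from markers is the second derivative of position. Filtering and differentiation are both linear, so smoothing the positions at 6 Hz reduces the derived acceleration by the same gain at each frequency. Slope and loading rate lose more than the peak, because they depend on still higher frequencies.

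The cameras sample at 250 Hz and could represent content up to 125 Hz, so the filter, not the sampling, sets the limit. The agreement statistics charge any difference from the reference to the device. A device that reads the shin correctly would be reported as reading too high, on a primary outcome.

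**Working it through.** The plan gives no derivation of the 6 Hz value, so there is no figure to reproduce. The check asks what the filter does to an impact pulse.

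**Inputs.** From the article: fourth order, 6 Hz, cameras at 250 Hz. Assumed, because the article does not give it: pulse duration, taken as 20–60 ms. Two shapes were used: a half-sine (width = total duration) and a Gaussian (width at half height).

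**Step 1, filter gain.** Single pass, fourth order: 1/√(1+(f/6)^8). Zero-lag, second order run forward and back: 1/(1+(f/6)^4).

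| f (Hz) | single pass | zero-lag |
|---|---|---|
| 6 | 0.71 | 0.50 |
| 10 | 0.13 | 0.11 |
| 12 | 0.06 | 0.06 |
| 15 | 0.03 | 0.03 |
| 20 | 0.01 | 0.01 |

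**Step 2, fraction kept at 6 Hz (zero-lag / single pass).**

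| Width (ms) | Half-sine peak | Half-sine slope | Gaussian peak | Gaussian slope |
|---|---|---|---|---|
| 20 | 0.17 / 0.18 | 0.02 / 0.03 | 0.27 / 0.30 | 0.06 / 0.09 |
| 30 | 0.25 / 0.27 | 0.04 / 0.06 | 0.39 / 0.43 | 0.14 / 0.18 |
| 40 | 0.32 / 0.36 | 0.07 / 0.10 | 0.50 / 0.55 | 0.22 / 0.29 |
| 60 | 0.46 / 0.51 | 0.15 / 0.20 | 0.66 / 0.73 | 0.41 / 0.49 |

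Running a fourth-order filter in both directions lowers the smallest peak figure slightly, to 0.16.

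Hand check: for a short pulse, the filtered peak is at most the pulse area times the peak of the filter's impulse response. For the zero-lag form that peak is 2 × 6 × ∫du/(1+u^4) from 0 to ∞ = 12 × 1.111 = 13.3 per second. A 20 ms half-sine of unit height has area 2 × 0.020/π = 0.0127 s, and 0.0127 × 13.3 = 0.17, as in the table.

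**Step 3, effect on agreement.** Suppose the reference keeps a fraction q of a true peak T with mean μ and SD σ, and the wearable is exact. Then:
- bias = (1−q)μ;
- limits of agreement widen by 1.96(1−q)σ on each side;
- r is unchanged by scaling;
- consistency ICC = 2q/(1+q²);
- absolute-agreement ICC = qσ² / [(σ²+q²σ²)/2 + (1−q)²μ²/2].

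The last depends only on q and σ/μ. With σ/μ = 0.25 (assumed; take μ = 8, σ = 2):
- q = 0.5: consistency 1/1.25 = 0.80; absolute 2/(2.5+8) = 0.19.
- q = 0.2: consistency 0.4/1.04 = 0.38; absolute 0.8/(2.08+20.48) = 0.04.

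A simulation with n = 40 and small added errors agrees: absolute ICC 0.04–0.19, consistency ICC 0.38–0.78, r 0.96–0.98.

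**Step 4, price of a higher cut-off.** For white marker noise of SD s sampled at 250 Hz, the variance of the derived acceleration is (s²/125) ∫(2πf)^4 H(f)² df from 0 to 125 Hz. With s = 0.5 mm (assumed) and a 50 Hz zero-lag filter, this gives an SD of about 1.6 g for exact differentiation. Simple second differences, which damp the highest frequencies, give about 1.1 g. At 6 Hz it is below 0.02 g. At 50 Hz the 20 ms pulse keeps 89–96% of its peak as a half-sine and at least 96% as a Gaussian. The half-sine slope keeps only 60–65%.

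**The case against.** **Pulse length is assumed.** True. At 80 ms a half-sine keeps 58–65% of its peak, and at 100 ms 69–76%. Its slope still loses at least 60% at 100 ms. Adding a slower stance component of 1–3 g under a 6 g impact of 20–60 ms leaves the filtered peak at 19–63% of the raw peak. The assumption governs the size of the loss more than its existence.

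**The wearable side is not known to be unfiltered.** This stands. The Wearables section says that commercial exports have usually passed through an algorithm. The loss in the reference follows from the text; the net bias depends on processing that is not shown. A reader might infer a definite error in g, but the documents give neither a typical peak nor the device bandwidth.

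**A reader might infer that treadmill contact, step and flight time are spoiled too.** Motion capture is their treadmill reference, but the article does not support this. Events are picked by eye ("Gait identification will be achieved through visual inspection of foot strike and toe off for consecutive strides over the 60s"), and nothing says that the assessor views filtered trajectories. The rise time of a smoothed step, about 75 ms, is not a timing error: under a zero-lag filter its midpoint hardly moves. Overground contact, step and flight times use force plates.

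**Scope.** One of eight Table 2 outcomes and two of three devices are affected. Wearable test-retest reliability, real-world agreement between devices, group comparisons and usability do not use this reference. Laboratory results are to be reported descriptively. The ICC bands are introduced for reliability, so they should not be borrowed to label validity.

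**The article is condensed.** It does not leave the cut-off open. It states one value, and that value conflicts with an outcome it also states.

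**Conclusion.** The point holds for tibial acceleration measured by DorsaVi and DANU. As written, the reference keeps roughly 17–73% of the peak for assumed 20–60 ms pulses. It keeps about 2–41% of the maximum slope with a zero-lag filter, up to 49% with a single pass. These ranges rest on the assumed pulse durations, the two shapes and the reading of the filter order. The absolute difference, Bland-Altman results, RMSE and an absolute-agreement ICC would largely measure the filter. Pearson's r and a consistency ICC would be less affected, and the article does not say which ICC form is meant. A high r beside a large bias could therefore be misread as device error. No figure in g, no effect on gait-event timing and no effect on other outcomes is established.

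**What to change.** 1. State in Data processing that the 6 Hz filter does not apply to tibial acceleration.
2. Reprocess the stored raw trajectories for this outcome with a cut-off chosen by residual analysis. Report both the signal kept and the noise after double differentiation.
3. Apply the same filter to the wearable signal wherever raw data exist. DorsaVi samples at 100 Hz, so a matched cut-off for it must lie below 100/2 = 50 Hz. The 50 Hz figures above are illustrative, not a recommendation.
4. If no cut-off gives an acceptable reference, do not call motion capture the criterion for peak, slope and loading rate. Report agreement between DANU and DorsaVi only, and say that it is not criterion validity.

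**Cost.** A short amendment to Data processing and Table 2 and a rerun on stored data, assuming that the unfiltered trajectories are kept; no new data collection. The real price is noise: roughly 1 to 1.6 g SD at 50 Hz if marker noise is 0.5 mm (assumed), so bias may be traded for wider limits of agreement. Under step 4 the study loses its criterion reference for part of one primary outcome.

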### Statistical analysis

#### Analysis common to all studies

The statistical analysis will be performed using statistical software SPSS 25 (SPSS Inc., Chicago, Illinois, USA). Demographic characteristics will be summarised using descriptive statistics, including mean, standard deviation, median, minimum, maximum, and inter-quartile range for continuous or ordinal data and percentages for categorical data. The descriptive statistics will be tabulated and presented graphically for clarity. All data will be checked for normality distributed with Shapiro-Wilks tests before conducting parametric tests. Non-normal continuous distributions will be transformed where appropriate to meet the requirements of parametric tests; otherwise, the equivalent non-parametric tests will be adopted. Data will also be assessed graphically (such as histograms or scatter plots) for clarity of information. Statistical significance will be determined at p < 0.05 unless otherwise stated. Due to the experimental nature and novelty of the work and wearable systems, we will not control for multiple comparisons in order to avoid a Type II error.

*Analytical validation analysis*. To examine analytical (concurrent) validation of the wearable devices (research-grade, commercial, novel multimodal) for running gait measurement, we will compare outcomes to relevant reference measures (i.e., force plates for ground contact time) in all laboratory testing participants (n = 40). To compare running gait outcomes from the wearables and reference systems, the absolute difference, Pearson’s correlation (r), intraclass correlations (ICC), the level of agreement through the Bland Altman plots, and 95% Limits of agreement (LoA) will be calculated [48]. Accuracy will be evaluated in terms of root mean squared errors (RMSEs).

To determine test re-test reliability of the wearables, r, and ICCs between the two testing time-points will be calculated [49]. A predefined ICC performance scale will be used, defined as poor (<0.50), moderate (0.50–0.75), good (0.75–0.90) or excellent (>0.90) [50]. ICC is a common statistic for evaluating repeatability and is needed to calculate the minimally detectable change (MDC) [51, 52]. The standard error of measurement (SEM) and standard deviation (SD) will also be calculated. Laboratory based analytical validity and reliability outcomes will be descriptively reported and discussed across research-grade, commercial and novel multi-modal wearable devices.

To examine the analytical (concurrent) validation of running gait outcomes measured in real-world settings from the various grades of wearables in all real-world testing participants (n = 40), we will compare outcomes across the wearable devices (research, commercial and novel multi-modal) through widely used measures of agreement. The absolute difference, r, ICC, the level of agreement through the Bland Altman plots, 95% LoA, RMSEs will be calculated to evaluate agreement between outcomes generated by each wearable [48].

*Exploratory clinical validation analysis*. To provide an initial exploration of clinical (performance) validation, we will investigate group difference and relationships with clinically (or performance) relevant measures. For group differences (e.g., previous injury history or performance level), analysis of co-variance (ANCOVA), will be conducted to assess for differences between groups (injured vs non-injured, or elite vs novice) in the individual running gait outcomes (e.g., ground contact time etc.) from the novel multimodal, commercial and research-grade wearable devices during the running tasks, while controlling for demographics that are significantly related to the running gait outcomes. Relationships between running gait outcomes and demographic variables (e.g., sex, age, height, weight etc.) within groups (injured vs non-injured, or elite vs novice) will be completed through Pearson correlations within each grade of wearable device (research, commercial, multimodal).

To examine the usability of the wearable devices the SUS scores for each wearable will be calculated and visualised. To investigate differences in participant perception of the usability for each grade of wearable, separate analysis of variance (ANOVA) tests will be performed. The ANOVAs will determine the differences between the SUS scores within the different device grades between participant groups (e.g., injury history, performance level). The relationships between the SUS scores, demographics (e.g., sex, age, age-grade performance), and wearables characteristics (e.g., price, weight, and battery life) will be explored using Pearson correlations [39]. The strength of the correlation will be assessed based on Cohen’s criteria: correlations < 0.30 are considered small, correlations between 0.30 and 0.50 will be considered medium, and correlations > 0.50 are considered strong [53].

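### The Shapiro-Wilk rule is applied to the data rather than to ANCOVA residuals, so it can trigger needless transformations or rank tests, and no covariate-adjusted fallback is named

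*Protocol article*

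**What the plan says.** The rule is in the Protocol article, Statistical analysis, under the heading on analysis common to all studies. It has three steps.

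1. Check: "All data will be checked for normality distributed with Shapiro-Wilks tests before conducting parametric tests".
2. Transform: "Non-normal continuous distributions will be transformed where appropriate to meet the requirements of parametric tests".
3. Fall back: "otherwise, the equivalent non-parametric tests will be adopted".

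Graphs are planned as well, but as presentation and not as the criterion: "Data will also be assessed graphically (such as histograms or scatter plots) for clarity of information". The significance level is 5% ("Statistical significance will be determined at p < 0.05 unless otherwise stated").

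Two later analyses are affected. For group differences, "analysis of co-variance (ANCOVA), will be conducted to assess for differences between groups (injured vs non-injured, or elite vs novice"), "while controlling for demographics that are significantly related to the running gait outcomes". This is done outcome by outcome for the data of each device, and no non-parametric counterpart to ANCOVA is named. For agreement, "the level of agreement through the Bland Altman plots, and 95% Limits of agreement (LoA) will be calculated", with no statement that the distribution of the device-minus-reference differences is checked and no alternative form of the limits. The Sample size calculation section gives 20 participants per group for the group comparisons and 40 for analytical validation.

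**The concern.** The rule looks at the wrong quantity. ANCOVA assumes that the outcome is roughly normal after group and covariates have been taken out. The outcome itself may be skewed because a covariate is skewed, or bimodal because two well-separated groups are pooled, while the residuals are perfectly well behaved. The rule would then call for a transformation or a rank test that is not needed. Because it is applied to each outcome on each device, one device could be analysed on the original scale, a second on a log scale and a third by ranks, for the same outcome in the same runners.

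The fallback matters because the groups (injury history, performance level) are not randomised and the plan intends to adjust for demographics. The common two-group rank test carries no covariates. Where it is used, the question changes from an adjusted to an unadjusted group difference.

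For agreement, the mean ± 1.96 SD form of the limits rests on the distribution of the paired differences. Normal readings on both systems say little about that.

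**Working it through.** The plan gives no effect size, SD or power for the group comparisons, so it has no figure of its own to reproduce. From the documents come 20 per group, 40 in total, α = 0.05 (taken as two-sided), ANCOVA with covariates, and limits of agreement. Everything else below is an assumption.

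**Group comparisons.** Assumed model, total within-group SD 1:

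Y = 0.8·G + 0.7·X + √(1 − 0.7²)·ε, with ε normal, so the residual SD is √0.51 = 0.714.

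X is either normal or skewed (exponential). The outcome CV is about 10%, which matters only for the log transform.

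Closed-form benchmark at 20 per group and d = 0.8: power is 71.6% unadjusted. With the SD reduced to 0.714 it is 94.3%, before allowing for the estimated slope and chance covariate imbalance. Simulation, 4,000 trials per setting, gives:

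| Quantity | Normal covariate | Skewed covariate |
|---|---|---|
| Shapiro-Wilk rejects the outcome | about 5% | about 20% |
| Shapiro-Wilk rejects the residuals | about 5% | about 5% |
| Still rejected after a log transform | about 3% | about 8% |
| Power, ANCOVA | 92–93% | 91–92% |
| Power, unadjusted rank test | about 68% | about 72% |

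In the skewed-covariate setting, applying all three steps of the rule, with an unadjusted rank test as the last step, gives average power of about 90% against about 91% for ANCOVA throughout. This fits simple arithmetic: about 8% of outcomes switch and each loses about 20 points (92 − 72), so 0.08 × 20 = 1.6 points on average.

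*Bias.* With the covariate 0.5 SD apart between groups, a covariate correlation of about 0.7 and no adjusted group effect, the unadjusted rank test is significant in about 18–20% of trials. ANCOVA stays at 5%.

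*Where the rule does no harm.* With a normal covariate, or with groups 2 SD apart, outcome and residuals are both rejected about 5% of the time. At 3 SD apart the outcome fails in about 26% and the residuals in 5%, but ANCOVA and the rank test both have 100% power, so none is lost.

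*Different verdicts across devices.* With three devices measuring the same quantity with independent noise (assumed SD 0.4) and a skewed covariate, the first Shapiro-Wilk step disagreed across devices in about 22% of outcomes. This is before any transformation.

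**Limits of agreement** (mean difference ± 1.96 SD, n = 40).

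- Normal readings (SD 25), skewed differences (shifted exponential, SD 8): the readings are flagged in about 6% of cases and the differences in 99.5%. With known parameters, the share above the upper limit is exp(−(1 + 1.96)) = exp(−2.96) = 5.2%. The lower limit, −1.96 × 8 = −15.7, lies below the smallest possible difference, −8, so nothing falls below it. With limits estimated from 40 participants the averages are 6.2% above and 0% below, against the intended 2.5% on each side.
- Skewed readings, normal differences: the reference readings are flagged in 99.7%, the wearable readings in 88.3% and the differences in 4.9%.

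The check on readings and the check on differences can therefore disagree in either direction.

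**The case against.** The case against is substantial, and much of it stands.

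- *Transformation comes first.* A reader might take the roughly 20% rejection rate as the rate of switching to rank tests. It is not: a log transform brings it to about 8%, or about 3% with a normal covariate, and a more flexible transform lowers it further. What remains is that the transformation is triggered by the same misdirected check, so it may be needless and may differ between devices.
- *Lost adjustment is not stated.* A reader might infer that the fallback always drops the covariates. The protocol leaves the equivalent test unnamed, and a rank-based ANCOVA would keep them. The supportable point is that no adjusted fallback is specified, so adjustment may be lost.
- *Limits of agreement are not gated.* A reader might infer that Shapiro-Wilk decides whether limits are reported. The rule governs parametric tests, and limits are estimates. Bland-Altman plots are planned in both settings and show skew or spread that grows with the mean. Only a stated alternative form of the limits is absent.
- *Device comparison as a whole is not undermined.* Analytical validity rests on agreement statistics that do not pass through ANCOVA, and the laboratory results are to be compared descriptively. The group comparisons are labelled exploratory.
- *All data need not mean raw outcome values.* That is the natural reading, but the word raw is not used.

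It could also be said that such detail belongs in a fuller plan. The article does not leave the matter open, however: it states a decision rule and the object of the check.

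**Conclusion.** The concern holds in a narrow form. As written, the normality rule targets the data rather than the ANCOVA residuals, so it can change an analysis that was sound, and differently by device for the same outcome. The average cost is small: about one percentage point of power (91% to 90%) once transformation is counted. The cost is concentrated in any outcome that ends in an unadjusted rank test. There, power is about 68–72% instead of 91–93%, and false positives run at about 18–20% instead of 5% if the covariate differs by 0.5 SD between groups. The contrast of about 92% with 68% describes an outcome that has switched; it is not the effect of the rule across the study.

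These sizes rest on an assumed covariate correlation of 0.7, an exponential covariate, normal residuals, d = 0.8 and an outcome CV near 10%. None of these is in the documents. With a normal covariate and moderate group differences, the misdirected check rarely matters. For limits of agreement, the check does not reach the relevant quantity, but the planned plots partly fill the gap. The point is worth fixing and is of minor weight, mainly for the exploratory group comparisons.

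**What to change.** Amend the statistical analysis wording as follows.

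- For the group comparisons, replace the Shapiro-Wilk gate with a check of the ANCOVA residuals, by plots first.
- Keep covariate-adjusted ANCOVA for every device. If residuals are clearly non-normal, use bootstrap confidence intervals or a rank-based ANCOVA, so that the adjustment is retained.
- Choose scale and method once per outcome and apply them to all devices that measure it.
- Use the Bland-Altman plots to judge the differences. Where these are skewed or grow with the mean, report log-ratio or percentile limits of agreement.

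The cost is a few sentences and a little more analysis work; no data collection or sample size changes.
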